# Rationale and design of the multicenter randomized trial investigating the effects of levosimendan pretreatment in patients with low ejection fraction (≤40 %) undergoing CABG with cardiopulmonary bypass (LICORN study)

**DOI:** 10.1186/s13019-016-0530-z

**Published:** 2016-08-05

**Keywords:** Coronary artery bypass graft, Low cardiac output syndrome, High risk surgical patient, Levosimendan, Cardiac surgery, Perioperative management

## Abstract

**Background:**

Patients with a left ventricular ejection fraction (LVEF) of less than 40 % are at high risk of developing postoperative low cardiac output syndrome (LCOS). Despite actual treatments (inotropic agents and/or mechanical assist devices), the mortality rate of such patients remains very high (13 to 24 %). The LICORN trial aims at assessing the efficacy of a preoperative infusion of levosimendan in reducing postoperative LCOS in patients with poor LVEF undergoing coronary artery bypass grafting (CABG).

**Methods/Design:**

LICORN study is a multicenter, randomized double-blind, placebo-controlled trial in parallel groups. 340 patients with LVEF ≤40 %, undergoing CABG will be recruited from 13 French hospitals. The study drug will be started after anaesthesia induction and infused over 24 h (0.1 μg/kg/min).

The primary outcome (postoperative LCOS) is evaluated using a composite criterion composed of: 1) need for inotropic agents beyond 24 h following discontinuation of the study drug; 2) need for post-operative mechanical assist devices or failure to wean from these techniques when inserted pre-operatively; 3) need for renal replacement therapy. Secondary outcomes include: 1) mortality at Day 28 and Day 180; 2) each item of the composite criterion of the primary outcome; 3) the number of “ventilator-free” days and “out of intensive care unit” days at Day 28.

**Discussion:**

The usefulness of levosimendan in the perioperative period has not yet been documented with a high level of evidence. The LICORN study is the first randomized controlled trial evaluating the clinical value of preoperative levosimendan in high risk cardiac surgical patients undergoing CABG.

**Trial registration number:**

NCT02184819 (ClinicalTrials.gov).

## Background

Patients with an ejection fraction of less than 40 % are at high risk of developing postoperative low cardiac output syndrome (LCOS) following cardiac surgery. The patients who develop this condition exhibit a very high mortality rate, ranging between 13 to 24 %, whereas those who are not affected by this complication have a mortality of 2 % only [1]. The LCOS is also associated with more frequent complications including pulmonary impairment, myocardial infarction, stroke, renal failure, and need for reoperation [2, 3]. Preventing LCOS is therefore a priority for anaesthesiologists working with cardiac surgical patients. The incidence of LCOS following coronary artery bypass grafting (CABG) surgery varies from 3 to 14 % [1], but the presence of a preoperative left ventricular dysfunction (i.e.: 20 % < left ventricular ejection fraction (LVEF) < 40 %) doubles the risk [1].

The therapeutic management of LCOS usually involves inotropic agents (catecholamines, phosphodiesterase inhibitors) as first-line treatment. Catecholamines may worsen myocardial oxygen imbalance and have been associated with an increase in morbidity and mortality after cardiac surgery [4]. Phosphodiesterase inhibitors such as milrinone are also associated with deleterious side-effects, such as hypotension and arrhythmia, and increased mortality in heart failure patients [4, 5]. New drugs that could help for the management of LCOS with a better tolerance profile are therefore highly desirable, in particular in view of the changing demographic profile of cardiac surgical patients whose severity at admission has steadily increased over the past years.

Levosimendan acts as an inotrope and a vasodilator via two different pathways. First, it induces a calcium-dependent binding to troponin C resulting in a “sensitization” of the myofilaments to calcium and a positive inotropic effect, without impairing myocardial oxygen balance. Second, it opens smooth muscle ATP-dependent potassium (K_ATP_) channels, thereby producing a vasodilatation. In addition, levosimendan also opens the mitochondrial K_ATP_ channels, an action that has been linked to a cardioprotective effect [6].

Several studies have suggested that levosimendan could be helpful to prevent LCOS and reduce morbidity and mortality after cardiac surgery [7–10]. Two recent meta-analyses on the perioperative use of levosimendan reinforce the idea of a potential benefit on outcomes, especially in patients with poor preoperative left ventricular ejection fraction [11, 12]. They also conclude that a large prospective randomized trial should be performed to confirm this hypothesis. The purpose of the “Levosimendan in coronary artery revascularization” (LICORN) trial is to verify the ability of levosimendan to prevent LCOS after CABG surgery in patients with poor left ventricular function.

## Methods/design

### Study population

We target the recruitment of patients aged over 18, scheduled for CABG surgery with cardiopulmonary bypass, who have a LVEF equal to, or less than 40 %, regardless of the method of assessment. The CABG may be combined (or not) with the repair of a valve or of another cardiac structure. The patients can be enrolled even if they receive preoperative inotropes, or if the surgeon decides to insert an intra-aortic balloon pump (IABP) prior to cardiopulmonary bypass, or if they have another left ventricular assist device in place. The exclusion criteria are listed in Table 1.

**Table 1 Tab1:** Exclusion criteria

Preoperative renal failure (creatinine clearance < 30 ml/min)
Liver failure (prothrombine time < 50 %, in the absence of vitamin K antagonist
Cardiac surgery without CABG
Pregnancy
Emergency surgery, defined as surgery within the 24 h of the operative indication
Known allergy to levosimendan
Severe hypotension prior to surgery (mean arterial pressure < 60 mmHg)
Severe tachycardia prior to surgery (heart rate > 120 bpm)
Prior history of torsade de pointe
Dynamic obstruction of the left ventricular outflow tract
Lack of signed informed consent
Lack of affiliation to social security
Patient already involved in another trial

### Study design

Thirteen cardiac surgical centers, including 12 University hospitals and 1 private hospital, have been invited to participate in the study. The study is a randomized, double-blind, two-arm parallel-group, placebo-controlled phase III study. The chronology of the protocol is depicted in the Figure. Patients will be followed until postoperative day 180.

### Study drug administration

The study drugs are stored at 2–8 °C until reconstitution using 500 ml of 5 % dextrose solution, immediately prior to patient administration. Physical and chemical stability of the preparation at room temperature is demonstrated up to 24 h following reconstitution [13]. The placebo is made of riboflavin in order to reproduce the yellow colour of levosimendan. No bolus is administered. A continuous infusion of 0.1 μg/kg/min is started just after anaesthesia induction and is administered over the ensuing 24 h in the absence of serious adverse reaction. Tables are provided to clinicians to determine the flow rate of the drug solution according to patient’s weight. The study drug administration is discontinued in case of serious adverse events such as: 1) anaphylactic reaction, 2) refractory hypotension defined as a mean arterial pressure (MAP) < 60 mmHg despite optimal therapeutic response comprising fluids and vasoconstrictors at the discretion of the clinician, 3) intractable arrhythmia.

### Randomization and blinding procedures

The allocation of treatments will be performed by minimization (deterministic dynamic allocation) [14]. The procedure will take into account the center, the surgery performed (CABG alone, or combined surgery), LVEF (<30 %, or between 30 and 40 %), the redo nature of the surgery, the existence of a treatment by preoperative inotropic agents or IABP, and the existence of preoperative beta-blocker therapy. It will balance the distribution of prognostic factors between the two groups and within each center. We will introduce a random component to reduce the predictability of the allocation.

We chose to use a minimization procedure because the stratified randomization is not effective in trials with small sample size and large number of strata. This is the case in the present study since the 3 factors that must be controlled (type of surgery, preoperative treatment, and LVEF range) would result in eight strata at all 13 centers.

The randomization algorithm will be established by an independent statistician. This algorithm will then be installed on a website with secure access. At randomization, the clinician will obtain the blinded patient allocation number after having provided the patient characteristics required by the algorithm. The result of the randomization will be sent to the pharmacy at the center involved.

### Outcome measures

The primary aim of the trial is to demonstrate that levosimendan administration at the time of anaesthesia induction in patients undergoing CABG (alone, or combined with other cardiac repair) with poor LV function (LVEF ≤ 40 %) can reduce the incidence and severity of postoperative LCOS. Our primary endpoint is a composite of three elements that reflect this syndrome:The need for inotropic agents beyond 48 h after the initiation of the study treatment infusion;The need for post-operative circulatory mechanical assist devices (intra-aortic balloon pump, extra-corporeal life support, left ventricular assist device such as the Impella® pump) or failure to wean from these techniques (at 96 h following initiation of the study treatment) if they were inserted pre-operatively;The need for renal replacement therapy (RRT) at any time during Intensive care unit stay (ICU).

The secondary goals are: 1) to compare mortality among placebo and levosimendan patients, and 2) to evaluate the effects of levosimendan treatment on ICU and hospital length of stay, as well as its impact on the duration of ventilation, and on each component of the primary composite endpoint separately. Thus, the secondary endpoints include:Mortality at Day 28 and Day 180 (safety issue)Individual components of the primary endpoint mentioned aboveNumber of days with mechanical circulatory assist devicesNumber of days with renal replacement therapy and number of RRT kits that are used for each patient.Number of ventilator-free days and out-of-ICU days at Day 28.

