### Statistics

#### Number of subjects required

The number of subjects required is 340 patients (170 per group). This sample size has been obtained using the Nquery Advisor statistical software according to the following assumptions:Incidence of the composite endpoint in the control group 65 % (proportion estimated from our personal data);Incidence of the composite endpoint in the levosimendan group 50 %. According to Levin et al. [15], postoperative administration of levosimendan in patients having a LCOS has reduced by 28 % the use of an additional inotropic drug and by 12 % the use of a mechanical assist device, compared to dobutamine.Alpha risk of 5 % and power of 80 %.

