#### Statistical analysis

The results will be presented in accordance with the CONSORT 2010 recommendations. Estimates of the primary and secondary endpoints incidence will be provided with their 95 % confidence interval.

The primary analysis will be done on an intention to treat basis, in all patients included in the trial and having undergone randomization.

Incidence of the unadjusted composite endpoint will be compared between the two groups using a Chi-square test. A multiple logistic regression model will compare the effects adjusted for LCOS prognostic factors: type of surgery performed (CABG alone, or combined surgery), LVEF (<30 %, or between 30 and 40 %), redo nature of the surgery, preoperative treatment with inotropic drugs or mechanical assist device and presence of preoperative beta-blocker therapy.

Three subgroups analyses are planned. They will assess whether the levosimendan effect varies according to:Type of surgical procedure performed (CABG alone or combined surgery)LVEF <30 %, or 30 % ≤ LVEF ≤ 40 %Presence of a preoperative treatment with beta-blockers.

The heterogeneity of the treatment effect will be evaluated by an interaction test and presented using a forest plot [16].

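### Death before 48 h without a post-operative device or RRT counts as a non-event on the primary composite, because the inotrope component can be met only by survivors to 48 h

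*Protocol article*

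**What the plan says.** All references are to the protocol article.

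- **Outcome measures, number of components:** "Our primary endpoint is a composite of three elements that reflect this syndrome". Death is not among the three. The Abstract also lists three components without death.
- **Component 1 (inotropes):** "The need for inotropic agents beyond 48 h after the initiation of the study treatment infusion".
- **Component 2 (devices):** any post-operative assist device, or "failure to wean from these techniques (at 96 h following initiation of the study treatment) if they were inserted pre-operatively".
- **Component 3 (RRT):** "The need for renal replacement therapy (RRT) at any time during Intensive care unit stay (ICU").
- **Outcome measures, secondary endpoints:** "Mortality at Day 28 and Day 180 (safety issue").
- **Statistical analysis, analysis set:** "The primary analysis will be done on an intention to treat basis, in all patients included in the trial and having undergone randomization".
- **Statistical analysis, test:** "Incidence of the unadjusted composite endpoint will be compared between the two groups using a Chi-square test".
- **Number of subjects required:** "Incidence of the composite endpoint in the control group 65" %, against 50 % with levosimendan, with 170 patients per group.

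The article nowhere says how a patient who dies before the 48 h or 96 h time point is classified on the composite.

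**The concern.** Component 1 depends on survival. A patient who dies at 30 h on inotropes never reaches the period in which the need for inotropes would count. If no post-operative device was placed and no RRT was given, no other component applies. The analysis set keeps this patient in the denominator, so the death is scored like an uncomplicated recovery.

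This conflicts with the aim in Outcome measures, which is to reduce both how often LCOS occurs and how severe it is. The Background gives mortality of 13 to 24 % in patients who develop LCOS and 2 % in those who do not, so an early death may be LCOS at its worst.

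Nor can equal early mortality in the two arms be taken for granted. The Discussion cites a randomised trial with mortality of 3.9 % on levosimendan and 12.8 % on placebo. In the other direction, Study drug administration names refractory hypotension and intractable arrhythmia as reasons to stop the 24 h infusion, which lies inside the 48 h window. An early survival benefit would be partly hidden by the composite, and early harm would be partly credited to the drug.

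**Working it through.** **1. The plan's own figure.** Inputs from Number of subjects required: p1 = 0.65, p2 = 0.50, alpha 5 % (taken as two-sided), power 80 %. The mean proportion is 0.575.

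n per group = [1.960 × √(2 × 0.575 × 0.425) + 0.842 × √(0.65 × 0.35 + 0.50 × 0.50)]² / 0.15² = (1.370 + 0.582)² / 0.0225 ≈ 169.3, rounded up to 170, or 340 in total.

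Power at 170 per group: the null standard error is √(2 × 0.575 × 0.425 / 170) = 0.0536 and the alternative standard error is √(0.4775 / 170) = 0.0530. Then Φ[(0.15 − 1.960 × 0.0536) / 0.0530] = 80.2 %. The sample size reproduces.

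**2. Who falls through.** Patients grouped by course, against the three components as written:

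| Course | Component met | Scored as |
|---|---|---|
| Post-operative device placed, then death at any time | 2 | event |
| RRT in ICU, then death at any time | 3 | event |
| Death after 48 h, inotropes needed beyond 48 h | 1 | event |
| Death before 48 h, no device, no RRT | none | non-event |
| Death before 96 h still on a pre-operative device, not on inotropes beyond 48 h, no new device, no RRT | depends on the reading of component 2 | ambiguous |

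The fourth row is the clear gap. The fifth is only ambiguous, because a patient who dies on the device was never weaned from it.

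**3. Effect on the estimate.** Let T be the true proportion with the composite when these early deaths are counted, d the proportion of such uncounted deaths, and C = T − d the proportion observed under the rule as written. Then

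C(placebo) − C(levosimendan) = [T(placebo) − T(levosimendan)] + [d(levosimendan) − d(placebo)].

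The bias equals the difference in uncounted early deaths, point for point. It is zero if the arms are equal.

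**4. Illustration with no true effect.** Assume T = 65 % in both arms. The death rates are assumptions; the documents give none.

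- d = 1 % placebo, 2 % levosimendan (1.7 and 3.4 patients of 170): observed 64 % against 63 %, a false benefit of 1 point. With null and alternative standard errors both 0.0522, the chance of a significant result favouring levosimendan is Φ[(0.01 − 1.960 × 0.0522) / 0.0522] = 3.8 %, where 2.5 % is nominal.
- d = 1 % placebo, 3 % levosimendan (1.7 and 5.1 patients): observed 64 % against 62 %, a false benefit of 2 points; the same chance is 5.7 %.

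**5. Cost of counting the deaths.** Taking 65 % and 50 % as rates for the composite as defined, and adding equal early deaths to both arms:

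- 1 % each: 66 % against 51 %, 169 per group needed, power at 170 per group 80.4 %.
- 2 % each: 67 % against 52 %, 167 per group needed, power 80.7 %.

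Counting equal early deaths needs no extra patients.

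**The case against.** The strongest reply has four parts.

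- **A rule may exist elsewhere.** The article condenses a fuller protocol and an analysis plan may exist; either could say how early deaths are scored. That is possible. But the article fixes the components with their time limits, and a rule making death an event would change that endpoint rather than fill in a detail.
- **The gap is narrow.** A new post-operative device counts with no minimum duration, and RRT counts at any time in ICU, so many dying patients will already be events. This stands, and it limits the size of the problem.
- **Harm would still be seen.** Mortality at Day 28 and Day 180 and each component are reported separately. This also stands. It protects the safety assessment but does not remove bias from the primary comparison.
- **The composite is meant to measure LCOS, not death.** This is a legitimate choice, and counting early deaths does bring in some from other causes, such as bleeding. It does not justify scoring a patient who dies on inotropes before 48 h as free of the syndrome.

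A reader might also draw three stronger conclusions that the documents do not support.

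- **That the trial is underpowered.** The 65 % and 50 % are stated for the composite as defined, so subtracting early deaths from them departs from the plan's inputs. Power on those inputs is 80.2 %.
- **That deaths before 96 h on a pre-operative device are certainly missed.** They can be read as failure to wean, and patients needing inotropes beyond 48 h are already events.
- **That a false benefit of several points is likely.** This would take, for example, 5 to 6 % of levosimendan patients dying early with neither device nor RRT. That exceeds the total levosimendan mortality of 3.9 % in the cited randomised trial, whose patients had LVEF below 25 %.

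**Conclusion.** The point holds in a limited form. As written, a death before 48 h without a post-operative device or RRT is a non-event on the primary endpoint. This follows from the stated components and the all-randomised analysis, on a literal reading and absent a rule in a document not shown. The 96 h weaning criterion is unclear rather than wrong.

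The number of patients affected cannot be derived from the documents and is probably small. The consequence is a bias equal to the between-arm difference in such deaths: 1 point for an assumed 1 % against 2 %, and none if the arms are equal. The sample size and its stated power are unaffected. The correction is still worth making, because the error favours whichever arm has more early deaths.

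**What to change.** Add to the primary endpoint definition, before unblinding:

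1. Death before 48 h after the start of the study infusion counts as meeting component 1.
2. Death before 96 h while still on a pre-operatively inserted device counts as failure to wean under component 2.
3. The composite without these rules is reported as a sensitivity analysis.

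The cost is a sentence or two in the endpoint definition, carried into the analysis plan. No added sample size is needed if early deaths are equal between arms. Deaths must already be ascertained for the Day 28 and Day 180 endpoints, but the article does not say that the hour of death is recorded, so the case report form should be checked for it. The downside is that a few early deaths unrelated to LCOS enter the composite; the sensitivity analysis shows how much they matter.

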### Data collection

After enrolment into the study, patients are assigned a unique subject number associated with their initials. Data are collected by investigators with the help of clinical research assistants and recorded on paper case report forms (CRF). A CRF must be completed for each participant. The data entered into each CRF will be assessed by sponsor representatives, according to good clinical practices. In addition to the patient’s medical file, the investigator agrees to complete the documents related to treatment management provided by the sponsor and the CRF at each step of the protocol (Fig. 1). All corrections and alterations of data on the CRF must be made by the investigator him/herself and highlighted according to predefined instructions. The data management will be carried out by the Clinical Research Unit of Hôpital Européen Georges Pompidou. A list of variables of interest will be developed with an Operational Data Model format by the study primary investigator and the study statistician. This list will allow the implementation of the case report form and of the database. A data-management plan, developed jointly by the study coordinator, the data-manager, and the statistician will be implemented. After correcting for potential errors detected by this plan, a data review meeting will be held to validate the entire database with the study coordinator. The database will then be frozen prior to statistical analysis. The data will be analysed using SAS software (SAS Institute Inc., Cary, NC).

**Fig. 1 Fig1:**
[figure not shown]
Schematic representation of the different steps of the LICORN protocol. LVEF: left ventricular ejection fraction; CABG: coronary artery bypass grafting; RRT: renal replacement therapy; ICU: intensive care unit

### Statistics

#### Number of subjects required

The number of subjects required is 340 patients (170 per group). This sample size has been obtained using the Nquery Advisor statistical software according to the following assumptions:Incidence of the composite endpoint in the control group 65 % (proportion estimated from our personal data);Incidence of the composite endpoint in the levosimendan group 50 %. According to Levin et al. [15], postoperative administration of levosimendan in patients having a LCOS has reduced by 28 % the use of an additional inotropic drug and by 12 % the use of a mechanical assist device, compared to dobutamine.Alpha risk of 5 % and power of 80 %.

